### Statistical analysis

Data analysis will proceed according to CONSORT guidelines for randomised controlled trials. The first stage of the analysis will be to use descriptive statistics to describe the group of individuals recruited to the trial in relation to those eligible, and to investigate comparability of the trial arms at baseline. The primary analyses will comprise three pair-wise intention-to-treat comparisons between decision analysis, information and usual care groups, for each of the two primary outcomes. These comparisons will use appropriate (that is, standard or logistic) multivariable regression models, adjusting for maternity unit, initial preference regarding mode of delivery, and value of the outcome variable at baseline. Full attention will be paid to the estimates and confidence intervals for these comparisons as well as the p-values, with the latter adjusted for multiple comparisons using Tukey's procedure. Secondary outcomes will then be analysed in the same way, using appropriate multivariable regression models depending on the nature of the outcomes.

Other secondary analyses will involve investigation of the short-term effects of the interventions using data from the two week follow up, and the effects at 36–37' weeks gestation adjusted for both baseline and two week follow up. Pre-planned subgroup analyses employing appropriate interaction terms in the regression models will be used to ascertain any differential effects of the interventions on the two primary outcomes across the following categories of women: previous caesarean section occurring before or after labour; previous successful vaginal delivery; stated preferred mode of delivery. Since the trial is powered to detect overall differences between the groups rather than interactions of this kind, the results of these essentially exploratory analyses will be presented using confidence intervals as well as p-values, and interpreted with due caution. Finally, we will investigate the effect of differential use of the information intervention via the internet using descriptive statistics and appropriate comparisons with the other groups.

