### Follow up

The primary and secondary outcomes are assessed in all three groups at baseline, and approximately two weeks after randomisation. The questionnaire at two weeks will constitute a secondary follow up, and will enable sufficient time for delivery of the appropriate interventions. As part of usual care, women in the trial normally attend the clinic at around 36–37 weeks' gestation to finalise plans for their preferred method of delivery. Questionnaire outcomes are measured again after this visit, and this constitutes the primary follow up for this trial. Actual and attempted mode of delivery (cross-checked with hospital records) and satisfaction with choice are assessed by a further postal questionnaire at approximately six to eight weeks after giving birth.

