### Justification of sample size

As noted above, differences in excess of 0.35 standard deviations have been considered as important for the total DCS score, and differences of this magnitude are feasible for interventions of this kind [23]. With regard to mode of delivery, UK data indicate that about 33% of women with one previous CS are delivered vaginally [1]. The sample size calculation for a previous trial of written versus verbal counselling in north America presumed a vaginal delivery rate of 30% for a minimal intervention, and in the event observed that 51% of women achieved vaginal delivery for the trial groups overall [20]. A change from 30–33% to 51% corresponds to an odds ratio of about 2.1–2.4, and this would certainly be considered as clinically important.

With two-sided 1% alpha, a total sample size of 600 provides 82–99% power to detect a standardised difference of 0.35–0.5 in total decisional conflict score between the groups, and 84–95% power to detect odds ratios of 2.1–2.4 in women achieving vaginal delivery. A pair-wise alpha of 1%, corrected for multiple comparisons using Tukey's procedure, maintains an overall study-wise alpha of 3.4%. In order to allow for pre-term deliveries, malpresentations, and losses to follow-up, we will therefore recruit 660 women to the trial.

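### The primary model adjusts mode of delivery for a baseline value that cannot exist; the covariates for that outcome should be named, and two planned subgroup variables would serve at little cost

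*Protocol article*

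**What the plan says.** The Statistical analysis section plans three pair-wise intention-to-treat comparisons for each of the two primary outcomes, by standard or logistic regression, "adjusting for maternity unit, initial preference regarding mode of delivery, and value of the outcome variable at baseline". Secondary outcomes are to be handled in the same way.

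The Outcome measures section names actual mode of delivery as the second primary outcome and attempted vaginal delivery as a secondary outcome.

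The Follow up section states: "The primary and secondary outcomes are assessed in all three groups at baseline, and approximately two weeks after randomisation". It then says that actual and attempted mode of delivery are obtained by postal questionnaire six to eight weeks after birth and checked against hospital records.

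Two items of obstetric history appear in the analysis plan only as exploratory interaction subgroups, next to stated preference: "previous caesarean section occurring before or after labour; previous successful vaginal delivery; stated preferred mode of delivery". The recruitment section stratifies allocation by maternity unit and preferred mode of delivery only.

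**The concern.** Women enter at about 12–20 weeks' gestation. Mode of delivery in the current pregnancy has no value then, nor two weeks later. One of the three covariates in the stated primary model is therefore undefined for one of the two primary outcomes, and the Follow up statement is untrue for that outcome and for attempted vaginal delivery.

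Two things are at stake. In a logistic model the covariate list partly defines the odds ratio being estimated, so it should not be left for the analyst to settle later. The vacant place could also be filled by variables likely to be informative about delivery, at almost no cost, and the plan uses them only for subgroups.

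**Working it through.** **1. Can any reading give the baseline term a value for mode of delivery?**

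- The outcome itself: no. It is observed at birth and recorded six to eight weeks later.
- Preferred mode at baseline: this is already a separate term in the same list, so it would be entered twice.
- Mode of the most recent delivery: the recruitment section requires this to have been a caesarean, so it is the same for every woman.

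The term therefore drops out. Maternity unit and initial preference remain, and these are the two stratification factors.

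**2. The plan's own power figures.** Inputs from Justification of sample size: "With two-sided 1% alpha, a total sample size of 600"; equal allocation is assumed, giving n = 200 per arm; z = 2.576.

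Decisional conflict, power = Φ(d√(n/2) − z):
- d = 0.35: Φ(3.5 − 2.576) = 82.2%
- d = 0.5: Φ(5.0 − 2.576) = 99.2%

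The article states 82–99%.

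Vaginal delivery, power = Φ{[p2 − p1 − z√(2p̄(1 − p̄)/n)] / √([p1(1 − p1) + p2(1 − p2)]/n)}, with p1 = 0.30:
- OR 2.1: odds 0.4286 × 2.1 = 0.900, so p2 = 0.474 and power is 84.3%
- OR 2.4: p2 = 0.507 and power is 95.4%

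The article states "84–95% power to detect odds ratios of 2.1–2.4 in women achieving vaginal delivery". All four figures reproduce, and none depends on the covariate list.

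The odds ratios are marginal: (0.51/0.49)/(0.33/0.67) = 2.11 and (0.51/0.49)/(0.30/0.70) = 2.43.

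**3. What would the two history variables add?** The article gives neither the prevalence nor the predictive strength of these variables, so the following are assumptions. Simulated logistic regression: 200 per arm, marginal rates held at 33% versus 51%, two-sided 1% Wald test, 3,000 replicates per setting. Initial preference is split 50/50, and the earlier caesarean came after labour in 60%. Maternity unit was not simulated.

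| Previous vaginal delivery: prevalence, OR | Caesarean after labour: OR | Preference: OR | Power, unadjusted | Power, preference only | Power, preference + both history terms | Gain (points) |
|---|---|---|---|---|---|---|
| 10%, 2 | 0.7 | 4 | 86.3% | 89.9% | 90.8% | 0.9 |
| 15%, 3 | 0.6 | 4 | 84.7% | 89.3% | 91.1% | 1.8 |
| 20%, 5 | 0.5 | 4 | 86.7% | 90.4% | 93.3% | 2.9 |
| 20%, 5 | 0.5 | 8 | 86.3% | 92.1% | 95.4% | 3.3 |

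The gain is the difference between the last two power columns. Taking the odds ratio for previous vaginal delivery up to 8 puts the upper end at about 4 points. The simulation error of a single power figure is about √(0.9 × 0.1/3000) = 0.5 points.

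**4. Validity and estimand.** With no treatment effect, rejection rates at the nominal 1% level were 0.8–1.4% across all three models, which is simulation noise. Under the alternative, the estimated odds ratio was 2.12–2.14 unadjusted, 2.30–2.52 with preference, and 2.37–2.79 with the history terms added.

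**The case against.** The strongest reply is that this is loose wording which corrects itself. The Follow up section goes on to separate questionnaire outcomes from mode of delivery, no analyst can enter a term that has no value, and what is left is a sound pre-specified model containing both stratification factors. No section promises to adjust for obstetric history, so leaving it out contradicts nothing. Much of this stands: dropping the empty term would not spoil the result. It does not remove the error, because the article does state the primary covariate set, and states it wrongly for one primary outcome.

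A reader might infer more: that omitting these predictors biases the odds ratio towards 1, or leaves harmful chance imbalance uncorrected. The documents do not support this. The smaller odds ratio reflects non-collapsibility, a different estimand, and the test's error rate already allows for chance imbalance under randomisation.

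A reader might also infer a gain of 2–8 points by comparing an unadjusted model with an adjusted one while fixing the conditional odds ratio at 2.1 (20% with a previous vaginal delivery, predictor ORs 3, 5 and 8: power 80%, 77% and 68% rising to 82%, 82% and 77%). That comparison ignores preference, which the plan already includes. It also lets the marginal odds ratio fall to 2.03, 1.96 and 1.88, a smaller effect than the planned 51%, and most of the loss comes from there.

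Two limits remain. That the history items are collected is inferred from the planned subgroups, since no section lists them as baseline data. That they predict mode of delivery is not stated either.

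**Conclusion.** The point holds in a limited form. The baseline-value covariate and the baseline-assessment statement are both impossible for actual and attempted mode of delivery. The delivery model that results, with maternity unit and initial preference, is valid. It forgoes a modest amount of precision: about 1–4 points of power at 33% versus 51%, 200 per arm and two-sided 1% alpha, with preference in the model. This assumes that 10–20% of women had a previous vaginal delivery, a predictor OR of 2–8 and a preference OR of 4–8. The stated 84–95% power stands either way. Correcting the two statements is necessary; adding the history terms is an efficiency recommendation.

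**What to change.** - **Statistical analysis:** limit adjustment for the baseline value to questionnaire outcomes that have one. For actual and attempted mode of delivery, pre-specify maternity unit, initial preference, previous vaginal delivery (yes/no), and previous caesarean before or after labour.
- **Follow up:** say that only questionnaire outcomes are assessed at baseline and two weeks.
- **Reporting:** label the adjusted odds ratio as conditional. It will be somewhat larger than the marginal 2.1–2.4 in Justification of sample size, and the two should not be compared directly.

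The cost is about one sentence in each section. No new data should be needed, since the planned subgroup analyses already require both variables; confirm that both are recorded for every woman from information that predates randomisation. The one small downside is the shift to an odds ratio conditional on more covariates.

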## Methods/design

### Recruitment and allocation of participants

The sample will comprise pregnant women with one previous lower segment CS (all parities will be included, but the most recent delivery must have been CS), no current obstetric problems and delivery expected at ≥ 37 weeks. Women are being recruited to the study by research midwives during their initial booking visit at approximately 12–20 weeks' gestation. Recruitment takes place from maternity units in St Michael's and Southmead Hospitals in Bristol, Weston General Hospital, and Ninewells Hospital in Dundee. The current CS rates for these units range between 18 and 24% and are representative of rates for other units throughout England and Scotland. The women are informed that although both vaginal delivery and repeat CS carry their own benefits and risks, the best method of presenting this information in order to assist women in reaching a decision is not known. Women expressing an interest in participating in the trial at the booking visit are given an information sheet, a written consent form and a baseline questionnaire to take home. Following receipt of the baseline questionnaire and written informed consent to enter the trial, women are randomised to one of three arms as detailed below. Allocation is stratified by maternity unit and preferred mode of delivery and blocked (using random permuted blocks of sizes 6, 9, 12 and 15) to ensure reasonable balance between the trial groups through time. The randomisation sequence was generated by a member of the study team ([name]), and allocation of participants is performed by a staff member with no other involvement in the study.

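### Single-step Tukey adjustment is valid, but with three arms a closed (step-down) version has more power at the same per-outcome family-wise error

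*Protocol article*

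**What the plan says.** The Statistical analysis section plans "three pair-wise intention-to-treat comparisons between decision analysis, information and usual care groups, for each of the two primary outcomes". It gives weight to estimates and confidence intervals "as well as the p-values, with the latter adjusted for multiple comparisons using Tukey's procedure". Grammatically, the adjustment applies to the p-values and not to the intervals.

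The Justification of sample size section uses "A pair-wise alpha of 1%, corrected for multiple comparisons using Tukey's procedure" and states that this "maintains an overall study-wise alpha of 3.4"%. Its power statements are per pair. On the DCS, for differences of 0.35 to 0.5 SD, it says: "With two-sided 1% alpha, a total sample size of 600 provides 82–99% power". On delivery, the corresponding claim is "84–95% power to detect odds ratios of 2.1–2.4 in women achieving vaginal delivery". No step-down or closed version is named, and one fixed pair-wise level for all three pairs is the single-step form.

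**The concern.** Single-step Tukey judges each of the three pairs as if all three null hypotheses might still be true. With three arms that protection is more than is needed once one difference has been established. If any two arms differ, at most one of the three equalities can hold, because any two equalities imply the third. Under the closure principle the remaining pairs can then each be tested at the full family-wise level, and strong error control is kept.

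What is at stake is efficiency. The trial compares each of two aids with usual care and with each other. When more than one true difference exists, a real second difference could be reported as non-significant under the single-step rule although an equally well controlled rule would have declared it.

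**Working it through.** **Inputs.** Two-sided pair-wise alpha 1%, 600 women analysed, DCS differences of 0.35 to 0.5 SD, and vaginal delivery rising from 30–33% to 51% (Justification of sample size). Three pairs per outcome and two primary outcomes (Statistical analysis). Equal arms of 200 are an assumption. It fits the allocation, which is "blocked (using random permuted blocks of sizes 6, 9, 12 and 15"), since all four sizes are multiples of 3.

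**1. The plan's own figures.** The expected z for a difference of 0.35 SD is 0.35 / √(2/200) = 3.5. Power = Φ(3.5 − 2.576) = 82.2%. For 0.5 SD, z = 5.0 and power = Φ(5.0 − 2.576) = 99.2%. For vaginal delivery from a 30% control rate, odds ratios of 2.1 and 2.4 give 84.3% and 95.4%. The stated 82–99% and 84–95% are reproduced as per-pair power.

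**2. Family-wise level.** A pair-wise critical value of 2.576 with three arms gives, from the studentised range, P(range > 2.576 × √2) = 2.70% per outcome.

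**3. The closed procedure at the same level.** Step one is unchanged: the largest absolute statistic must exceed 2.576. Step two tests each other pair at 2.70%, critical value 2.211. (With 597 degrees of freedom these are 2.584 and 2.217.) A pair's step-down p-value is the larger of the Tukey p-value of the most extreme pair and the pair's own unadjusted p-value. Neither can exceed that pair's single-step Tukey p-value, so the step-down p-value is never larger.

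**4. Power, both aids 0.35 SD better.** The two statistics against usual care have correlation 0.5 because they share that arm. Let J(a, b) = P(Z₁ > a, Z₂ > b) with both means 3.5.
- Single step, both aids: J(2.576, 2.576) = 71.8%.
- Step-down, both aids: 2 × J(2.211, 2.576) − J(2.576, 2.576) = 2 × 0.7709 − 0.7181 = 82.4%.
- Simulation with 597 degrees of freedom (2 million trials): 71.4% to 82.1%.
- Each comparison with usual care, same simulation: 82.0% to 87.3%.
- At least one difference among the three pairs: 92.5% under both methods, because step one is identical.

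**5. Other scenarios (power to show both aids better).**

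| Scenario | Single step | Step-down |
|---|---|---|
| DCS, both aids 0.5 SD | 98.5% | 99.4% |
| DCS, aids 0.35 and 0.5 SD | 81.8% | 89.8% |
| Vaginal delivery 33% vs 51% in both aids | 77.3% | 87.1% |
| Vaginal delivery 30% vs 51% in both aids | 92.6% | 96.7% |

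With aids at 0.35 and 0.5 SD, power for aid versus aid rises from 14.0% to 23.7%.

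**6. Error.** Under the global null both methods reject at least one pair 2.7% of the time. With one truly equal pair and the third arm far away, single-step rejects that pair 1.0% of the time and the step-down 2.7%. The maximum family-wise error per outcome is therefore the same, and the step-down uses an allowance that the single step leaves idle.

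**7. Sensitivity to the stated 3.4%.** That figure does not follow from three tests at 1%: Tukey gives 2.70%, independence 2.97%, and Bonferroni at most 3.0%. If 3.4% is taken as the family-wise level for both methods, power to show both aids at 0.35 SD goes from 74.8% to 84.8%, so the gain is again about 10 points.

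**The case against.** **Nothing here is an error.** This stands. Single-step Tukey is standard, controls error, and delivers the stated per-pair power. A reader might infer that the planned adjustment is faulty or that the trial is underpowered. The documents support neither.

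**The larger gain uses a goal the protocol does not set.** This also stands. The protocol powers each pair and plans three separate comparisons; it nowhere makes success depend on both aids beating usual care. On its own metric the gain is 82% to 87%. A reader might take 72% to 82% as the trial's shortfall, but it describes a joint aim chosen for illustration, at the lower end of the effect range. Nothing in the documents says that both aids helping equally is the likeliest result.

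**"Same error" needs qualifying.** This stands too. The maximum per-outcome error is equal, but the error for a single truly equal pair is not (1.0% against up to 2.7%). Control is also per outcome. If the two primary outcomes are taken as independent and the aids are equal to each other but both better than usual care, the chance of a false aid-versus-aid claim on either outcome goes from 1 − 0.99² = 2.0% to 1 − 0.973² = 5.3%. Under the global null both methods give about 5.3%.

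**Single-step Tukey has matching simultaneous intervals.** This is the main reason to keep it, but it carries limited weight here because the plan adjusts only the p-values and promises no simultaneous intervals.

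**An unseen analysis plan might name a step-down variant.** It might. What the article fixes, one 1% level for every pair, is the single-step form.

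**Conclusion.** The point holds as an optional, low-cost improvement. The planned method is valid; for p-values alone, the closed three-arm version is at least as powerful in every case and has the same maximum family-wise error per primary outcome. At 200 per arm and 0.35 SD in both aids, the gain is about 5 points per comparison and about 10 points for showing both. It is about 1 point for showing both at 0.5 SD, and nil for finding at least one difference.

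These sizes assume equal arms, 600 women analysed, and no power gained from covariate adjustment. The ordering of the p-values does not depend on the assumed effects.

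**What to change.** In the Statistical analysis section, replace the reference to Tukey's procedure with wording such as: *For each outcome, the pair with the largest absolute test statistic receives its Tukey-adjusted p-value; each other pair receives the larger of that p-value and its own unadjusted p-value.* Rank by test statistic and not by size of difference, because in covariate-adjusted or logistic models the standard errors differ between pairs. For the logistic models use Wald statistics; error control is then asymptotic.

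The version must be the closed one for three arms. An ordinary Holm step-down, which ignores that two equalities imply the third, reaches only about 75% for both aids at 0.35 SD.

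The cost is one sentence and trivial code, with no further women or data, and the change should be made before unblinded analysis. State three limits alongside it: a single truly equal pair may be falsely declared different up to 2.7% of the time instead of 1.0%; p-values reached at the second step have no matching simultaneous interval, so such an interval may just include no difference; and error is controlled within each primary outcome, not across the two.

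### A secondary analysis adjusts the 36–37 week effect for the two-week score, itself a result of the interventions, so its coefficient is neither the 36–37 week effect nor a randomised estimate of later effect

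*Protocol article*

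**What the plan says.** All references are to the Protocol article.

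- **Timing (Follow up).** Outcomes are "assessed in all three groups at baseline, and approximately two weeks after randomisation". On the two-week measure the section states: "The questionnaire at two weeks will constitute a secondary follow up, and will enable sufficient time for delivery of the appropriate interventions". For the later measure, taken once the 36–37 week clinic visit is over, it states: "Questionnaire outcomes are measured again after this visit, and this constitutes the primary follow up for this trial".
- **Primary model (Statistical analysis).** The three pair-wise intention-to-treat comparisons use regression "adjusting for maternity unit, initial preference regarding mode of delivery, and value of the outcome variable at baseline". No covariate is measured after randomisation.
- **Secondary models (same section).** "Other secondary analyses will involve investigation of the short-term effects of the interventions using data from the two week follow up". The same sentence then adds the effects at 36–37 "weeks gestation adjusted for both baseline and two week follow up".

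The article does not say what this last analysis is meant to estimate or how its coefficient is to be read. The caution that the section attaches to exploratory results concerns the subgroup interactions, not this analysis.

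**The concern.** Within one sentence the two-week score is first an outcome on which the interventions may act, and then a covariate for the later outcome. Holding it fixed has two consequences.

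1. Any part of the 36–37 week difference that was already present at two weeks, and is predicted by the two-week score, is taken out of the arm coefficient. An aid that works early and keeps its effect gets a smaller coefficient than one that works late.
2. Women with the same two-week score in different arms are no longer comparable by randomisation. Whatever else drives both scores, such as support from family or other information sources, differs between arms within levels of the two-week score if the intervention moved that score.

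At stake is a second figure at the primary time point that a reader could take for the intervention effect, set beside a primary result that it may seem to contradict. It could also separate the two aids wrongly if their effects develop at different speeds. That is plausible, because the information arm keeps internet access after the appointment, while the decision analysis is described as a session with a printout (Interventions).

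**Working it through.** **Inputs from the document.** The SD of the Decisional Conflict Scale (DCS) is 15 points, and 0.35–0.5 SD is 5.25–7.5 points (Outcome measures). The power statement is "With two-sided 1% alpha, a total sample size of 600 provides 82–99% power to detect a standardised difference of 0.35–0.5" (Justification of sample size). Equal allocation is assumed, giving 600/3 = 200 per arm.

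**Inputs not in the document (assumed).** These are d2, the slope b and the correlations between scores. Ranges are shown.

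**Step 1: the plan's own figure.** Power ≈ Φ(d·√(n/2) − 2.576), with √(200/2) = 10.
- d = 0.35: Φ(3.5 − 2.576) = Φ(0.924) = 82.2%.
- d = 0.5: Φ(5.0 − 2.576) = Φ(2.424) = 99.2%.

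The stated 82–99% reproduces. It does not depend on the secondary model.

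**Step 2: what the adjusted coefficient is.** Let d2 and d36 be the baseline-adjusted effects at the two times, and b the within-arm slope of the 36–37 week score on the two-week score given baseline. In a linear model the arm coefficient adjusted for both earlier scores is

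d36 − b·d2.

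**Step 3: size in points, with d36 = 5.25.**

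| Two-week effect d2 | b = 0.3 | b = 0.5 | b = 0.7 | Shortfall from d36 |
|---|---|---|---|---|
| 0 | 5.25 | 5.25 | 5.25 | 0% |
| 2.625 (half) | 4.46 | 3.94 | 3.41 | 15–35% |
| 5.25 (equal) | 3.68 | 2.63 | 1.58 | 30–70% |

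For example, 5.25 − 0.3 × 2.625 = 4.46 and 5.25 − 0.7 × 5.25 = 1.58.

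**Step 4: the same result from assumed correlations.** With r01 (baseline, two weeks), r02 (baseline, late) and r12 (two weeks, late) and equal SDs, b = (r12 − r01·r02)/(1 − r01²). Take d2 = d36 = 0.35 SD, 200 per arm and two-sided 1% alpha.

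| r01, r02, r12 | b | Adjusted coefficient | Share of d36 kept | Power, baseline-adjusted | Power, two-week-adjusted |
|---|---|---|---|---|---|
| 0.5, 0.4, 0.3 | 0.13 | 0.30 SD | 87% | 89% | 78% |
| 0.5, 0.4, 0.5 | 0.40 | 0.21 SD | 60% | 89% | 46% |
| 0.3, 0.3, 0.5 | 0.45 | 0.19 SD | 55% | 86% | 38% |
| 0.6, 0.5, 0.7 | 0.63 | 0.13 SD | 38% | 93% | 24% |

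A large simulation of the second row gave 0.349 SD without the two-week covariate and 0.212 SD with it. The formula gives 0.35 − 0.40 × 0.35 = 0.21.

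**Step 5: is it at least the later effect?** Suppose a fraction c of the two-week effect is truly carried forward through the two-week score. The effect not carried by that score is then d36 − c·d2, and the coefficient misses it by (c − b)·d2. The slope b equals c only if baseline and the other covariates capture every shared cause of the two scores. In the limiting case c = 0, where the scores correlate only through shared causes, none of the 5.25 points is carried by the two-week score. With d2 = 5.25 and b = 0.3–0.7 the model would still report 3.68 to 1.58.

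**Step 6: comparing the two aids.** Assume both have d36 = 0.35 SD, with d2 = 0.20 SD in one and 0.50 SD in the other, and b = 0.4. The adjusted effects are 0.35 − 0.08 = 0.27 SD and 0.35 − 0.20 = 0.15 SD. The gap of 0.12 SD (1.8 points) lies between two aids that are equally effective at 36–37 weeks.

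**The case against.** The strongest reply is that the total effect at 36–37 weeks is already the primary result, from a model with baseline covariates only. The two-week-adjusted model could then be a deliberate decomposition: first the short-term effect, then what is added later. The design gives reason to ask that, because website access continues and both intervention arms receive a letter at 35 weeks prompting discussion with clinicians. On that reading, removing the early effect is the purpose.

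Much of this stands. A reader might infer that the trial's main estimate is attenuated, or that an effective aid would be declared ineffective at the primary time point. The document does not support either inference, because the primary comparison has no post-randomisation covariate. Mode of delivery, the other primary outcome, is not named in this analysis. A reader might also infer that the model is meant to estimate the total effect. The wording, which speaks simply of effects at 36–37 weeks, invites that reading, but the article states no aim. Nor can a 30–70% loss be stated without conditions: it needs the full effect to be present at two weeks and b of 0.3–0.7.

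The decomposition reading does not rescue the model, however. Step 5 shows that it estimates the later effect without bias only if the two scores share no unmeasured cause, which randomisation cannot secure. The document neither states that assumption nor limits the interpretation. Nor is this a detail awaiting an unseen analysis plan, because the article itself specifies the adjustment.

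**Conclusion.** The concern holds in a limited form. A stated secondary analysis conditions on a post-intervention score, and its coefficient answers neither of the two questions it might be put to. The primary 36–37 week comparison and the power figures are unaffected.

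The distortion is conditional. For d36 = 5.25 points and assumed b of 0.3–0.7, the coefficient falls short of d36 by nothing if there is no two-week effect, by 15–35% if half of the effect is present by then, and by 30–70% if all of it is. These figures rest on a linear model with a common slope across arms. The risk is a misleading second estimate at the primary time point, not a wrong primary conclusion. The change should be made, but the trial's main inference does not hang on it.

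**What to change.** Replace the two-week-adjusted analysis with one repeated-measures (mixed) model of the two-week and 36–37 week questionnaire scores. Use baseline score, maternity unit and initial preference as covariates, and include an arm-by-time interaction. Report the effect at each time and the change in effect between them, for each pair of arms. All of these are contrasts between the randomised groups.

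If the two-week-adjusted model is kept, label it exploratory and describe it as an estimate of effect not carried by the two-week score, subject to there being no unmeasured shared causes. Do not report it as the intervention effect at 36–37 weeks.

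The cost is a change of wording and slightly more modelling, on data already planned for collection. One thing is given up: the change in effect, d36 − d2, answers a somewhat different question from the conditional one.
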